### Statistical analysis

Previous studies on the use of PCA have demonstrated that hospitalisation rates are seldom normally distributed. In essence, few patients will use the possibility to admit themselves to inpatient care, resulting in data that is positively skewed and has a leptokurtic distribution. Investigating whether assumptions of normality are violated will therefore be essential prior to any statistical analysis, whereby suitable means of analysing the data will be employed, that is, non-parametric tests or bootstrapping procedures. As for the self-reported outcomes, no prior evidence seems to suggest that data will not be normally distributed. Here, conditional changes over time will instead be modelled using a mixed models-approach, that is, multilevel models. All analyses will be made according to an intention-to-treat principle, accounting for those values that have been lost via multiple imputation or maximum likelihood estimation. Likewise, all analyses will control for potential confounders, such as hospitalisation rates prior to PCA and self-reported outcomes when assigned PCA, as well as demographics available in the hospital records, for example, age, gender, civil status, children and psychiatric disorders.

Apart from studying the results of introducing PCA, this study will also assess its cost-effectiveness, similar to a newly published study from Denmark.^10^ This includes determining the direct and total healthcare costs prior to and after being assigned PCA. Direct costs are the expenditures associated with each visit to a psychiatric emergency department, inpatient care and involuntary care. Such expenditures are calculated from standardised price estimates provided by Region Stockholm, resulting in an approximation of how expenditures change following the implementation of PCA. Total healthcare costs are the expenditures of other types of healthcare, for example, visits to primary care. Moreover, cost–utility analyses will also entail so-called quality-adjusted life-years (QALYs), which represent the improvement in terms of well-being for each incremental increase in costs by allowing patients to admit themselves, that is, a cost–utility approach. QALYs can be derived from self-reported outcomes on the EQ5D-5L, which is commonly used for this purpose, using population-generated preference weights which are available for a Swedish setting.^27^ This will be compared to matched patients using registries. In addition, probability sensitivity analyses will be conducted to determine the errors that surrounds the cost-utility calculations made. This provides confidence ellipses at 50%, 75% and 95% that represent the uncertainty associated with each estimate.

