#### Primary research question

For patients with severe psychiatric conditions, identified as having extensive care needs and who have been assigned PCA by their healthcare providers; how will their hospitalisation rates change during the following 12, 24 and 36 months with regard to the number of admissions and days in inpatient care, and the number of admissions and days in involuntary care?

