#### Secondary research question

Will hospitalisation rates differ between the various patient groups who have been assigned PCA?Will self-reported outcomes change following the assignment of PCA, that is, symptoms, quality of life and autonomy?Will self-reported outcomes differ between the various patient groups who have been assigned PCA?How are the healthcare expenditures for patients who have been assigned PCA affected, and do they differ between the various patient groups?What are the experiences of patients who have been assigned PCA for at least 12 months?What are the experiences of healthcare providers who have worked with PCA for at least 12 months?For adolescents, what are the experiences of caregivers to patients who have been assigned PCA for at least 12 months?For adolescents, will self-reported outcomes change in terms of their caregivers’ perception of the patients’ symptoms and quality of life?

In line with prior research, this study hypothesises that (1) the hospitalisation rates of patients will increase in terms of number of admissions to inpatient care, but (2) decrease in terms of days in inpatient care, as well as number of admissions and days in involuntary care. Furthermore, self-reported outcomes are expected to demonstrate (3) a decrease in symptoms and (4) increase in quality of life and autonomy. Lastly, qualitative investigations are believed to give a greater understanding of how patients, caregivers of adolescents and healthcare providers experience the use of PCA.

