### Study design

This study will evaluate the effects of PCA in Region Stockholm in collaboration with the Commissioner of Healthcare. This follows a resolution made by the popularly elected Region Stockholm Assembly, which means that both the implementation and policy surrounding PCA have already been decided. Hence, according to the decision, all patients with severe psychiatric conditions who are considered by their healthcare providers to have great care needs will be offered PCA as long as the criteria mentioned above are fulfilled. Furthermore, because the primary objective of the PCA programme is the provision of healthcare and not research, a more complex study design using randomisation on an individual or clinic level (ie, cluster) is not allowed due to ethical and judicial reasons. Hence, this study is restricted to a naturalistic prospective study design. Patients are followed for 12, 24 and 36 months using their medical records to check changes in hospitalisation prior to (pre) and following inclusion in the PCA programme (post), similar to what has been done previously.^7^ For example, patients who are included in November 2021 may have hospitalisation rates retrieved from the period November 2018–2020 and compared against hospitalisation rates from the period November 2022–2024, depending on the availability of historical data. In terms of self-reported outcomes, patients complete the measures when being assigned PCA and at the yearly follow-up assessments, with the exception for the VAS that is administered monthly via SMS. However, in these specific cases, historical data do not exist as these measures have not been collected previously. Only patients with no previous use of PCA when they consent to take part in this study will be analysed, as recorded in their hospital records.

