### Sample size calculation

This study intends to examine the impact of introducing PCA in psychiatric care in Region Stockholm. As such, only patients who are assigned PCA and have consented to take part in the research are included. An a priori sample size calculation, which is typically used to estimate an adequate sample size for subsequent recruitment, is thus not informative. However, based on previous experiences of introducing PCA in the region, it is reasonable to expect about twelve patients per inpatient ward who consent to participate, which would amount to a total sample size of 564.^7^ When calculating the standardised effect size possible to detect under these circumstances, based on the difference between two dependent means, and using a probability level of 0.05 and a power of 0.80, the result is Cohen’s *d* of 0.12, which is a small, although clinically relevant effect for a population of patients with severe psychiatric disorders, and in line with similar findings on self-reported outcomes.^4 8 9^

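### The primary hospitalisation analysis is chosen after a normality check between two routes that answer different questions, and the standard paired rank-test route breaks the plan's own adjustment rule

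*Protocol article*

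**What the plan says.** The Primary research question names four outcomes: "the number of admissions and days in inpatient care, and the number of admissions and days in involuntary care", over 12, 24 and 36 months. The design is a single group compared before and after assignment, without randomisation. The hypotheses, under Secondary research question, expect more inpatient admissions but a "decrease in terms of days in inpatient care, as well as number of admissions and days in involuntary care".

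Statistical analysis says that few patients will admit themselves, "resulting in data that is positively skewed and has a leptokurtic distribution". Normality is to be examined before any analysis, "whereby suitable means of analysing the data will be employed, that is, non-parametric tests or bootstrapping procedures". No test, effect measure or rule for choosing between the two is given. Mixed models are assigned to the self-reported outcomes only. The paragraph ends with rules for every analysis: missing values go to multiple imputation or maximum likelihood, and "all analyses will control for potential confounders, such as hospitalisation rates prior to PCA and self-reported outcomes when assigned PCA", together with demographics and diagnosis.

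The next paragraph of that section builds direct costs from emergency visits, inpatient care and involuntary care. Sample size calculation gives a detectable d of 0.12 "based on the difference between two dependent means".

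**The concern.** The two permitted routes are not two ways of answering one question. A bootstrapped mean change estimates how many days or admissions were gained or lost per patient. A signed-rank test asks whether changes, weighted by rank, lean up or down. With skewed use these can disagree. Under Procedure, a self-admission typically lasts up to 4 days, so PCA can add a few days for some patients while any large saving comes from long stays in a few others.

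Three things are at stake. The quantity tested for the primary outcomes is settled after the data are seen. If the plain rank route is taken, the adjustment rule is broken. And the statement on inpatient days could disagree with a cost result computed from the same days.

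**Working it through.** **The plan's own figure.** With N = 564, two-sided alpha 0.05 and power 0.80, d = (1.960 + 0.842)/√564 = 2.802/23.75 = 0.118, which rounds to the stated 0.12. The figure reproduces, and it is a paired-means calculation.

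**Adjustment rule against each route.**
- Signed-rank or sign test: the input is one difference per patient and there is no covariate term. Prior hospitalisation is already the pre side of the difference. The rule is not met.
- Bootstrap: any estimator can be resampled, including a regression-adjusted mean change. The rule can be met.

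**Can rank and mean disagree at this N?** Constructed example with assumed changes: 384 patients +4 days, 85 patients −30 days, 95 unchanged (total 564).
- Mean change = (384×4 − 85×30)/564 = (1,536 − 2,550)/564 = −1.80 days; SD 11.98; t = −1.80/(11.98/√564) = −3.56, p = 0.0004.
- Ranks: the 384 gains share mean rank 192.5, so W+ = 384×192.5 = 73,920. The 85 losses share mean rank 427, so W− = 85×427 = 36,295. Signed-rank p = 5×10⁻¹², in the direction of an increase.
- Bootstrapped mean change adjusted for two simulated covariates: −1.79 (95% interval −2.81 to −0.80). This route keeps the direction of the mean.

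**How often?** All inputs except N are assumed. Light users are 80% of patients and average 6 days; heavy users are 20% and average 90. Heavy use falls 30%. A share of light users (the uptake) adds a fixed number of days. The two periods are drawn independently from a negative binomial with dispersion 1 or 2. Mean change = 0.8 × uptake × added days − 0.2×90×0.30, the last term being 5.4. Ranges span repeated sets of 300–400 runs and both dispersions.

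| Uptake, added days | Mean change | Signed-rank: significant increase | Signed-rank: significant decrease | Paired mean: significant decrease |
|---|---|---|---|---|
| 50%, +6 | 2.40 − 5.4 = −3.0 | 95–98% | 0% | 28–48% |
| 30%, +8 | 1.92 − 5.4 = −3.5 | 68–77% | 0% | 33–62% |
| 20%, +8 | 1.28 − 5.4 = −4.1 | 16–30% | 0% | 46–75% |
| 10%, +8 | 0.64 − 5.4 = −4.8 | 0–3% | 1–7% | 51–90% |

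**Sensitivity to the assumptions.**
- Light users' regular days also fall 20%: at 20% uptake, false increases drop to 0–1%.
- Each patient keeps one underlying rate and the periods differ only by Poisson variation: false increases are 63–87% at 50% uptake, 1–8% at 30% and 0% at 20%. At 10% the signed-rank test finds the fall in 96–100% of runs.
- Each patient has a personal rate plus large period-to-period variation: false increases are 82–88% at 30% uptake, 27–43% at 20% and 1–6% at 10%. At 10% the signed-rank test finds the fall in 4% of runs or fewer, the paired mean comparison in 32–73%.
- A different model varies the heavy-user share (mean 80 days, use −40%; 70% of the others gain a Poisson number of days with mean 4). False increases are 99.8% with 15% heavy users, 51% with 20% and 1% with 25%. With 30%, the test reports a decrease in 96%. Its 70% of gainers is far above few.

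**The case against.** A reader might infer that the outcomes will be rank-tested and that the two rules of the paragraph cannot both be followed. The text does not support this: bootstrapping is offered as an equal alternative and can carry covariates. It names no rank test either. The signed-rank or sign test is the ordinary reading for paired data, and the exact test is the kind of detail a SAP may hold. That objection stands as far as naming a test goes. It does not remove the point, because the article itself states both the selection rule and the adjustment rule.

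A reader might also infer that the conclusion on days would have the wrong sign. That is not supported either. The protocol expects few self-admitters, and at 10% uptake reversal is rare.

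Other strong readings fall as well. Rank-based methods with covariates exist (rank ANCOVA, rank regression), so the conflict is with the standard paired tests. Unequal follow-up could be handled by ranking rates per unit of time. Treatment of unchanged patients depends on the variant used. The hypotheses do not name a mean, and the d of 0.12 is compared with findings on self-reported outcomes, so it does not by itself fix the mean as the hospitalisation target.

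**Conclusion.** The point holds in a limited form. The plan lets a normality check, whose outcome it already expects, open a choice between two routes with different targets. One of them, in its standard paired form, cannot meet the adjustment rule and need not agree with the mean or total days that drive costs. The conflict with the adjustment rule follows from the text alone.

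The size does not, because the documents give no rates or variances for hospital use. With large variation between a patient's two periods, reversal is common at 30% uptake, occasional at 20% and rare at 10%. At 10% the usual harm is a missed fall in mean days rather than a wrong sign. With stable patients even that harm disappears. So the route can decide whether the hypothesis on days appears supported, but whether it would do so here cannot be known from the protocol. Since these are the primary outcomes, the choice should be fixed before analysis.

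**What to change.** Remove the normality check as the selector. For all four hospitalisation outcomes, name one covariate-adjusted, mean- or rate-based pre/post analysis in advance. Two options are sound:
- a log-link count model with within-patient periods, a person-time offset and robust or bootstrap intervals, giving a post/pre rate ratio;
- a bootstrapped covariate-adjusted mean change per unit of person-time, giving an absolute difference.

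These are different effect measures, so one must be declared primary. State how prior hospitalisation enters, since it is already the pre side of the comparison. Keep rank tests as description only.

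The cost is one paragraph of wording and no new data. The downside is that intervals for mean days may be wide because of the skew.

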### Procedure

Patients who are eligible to receive PCA are invited to a scheduled meeting with their healthcare providers from the outpatient unit and inpatient ward. The purpose and practice of PCA are then discussed verbally and information is provided in writing. Should the patient accept the offer, an agreement on the use of PCA is reached collaboratively and recorded in their medical records. For adolescents, caregivers also have to agree. Typically, PCA involves up to 4 days of inpatient care at a time, up to three times per month, although exceptions to the rule can sometimes be made. The agreement only covers 12 months at a time, after which it can be renewed at the yearly assessments. After the meeting, the patient receives all of the details in text and a printed copy of the agreement.

Each inpatient ward has allocated at least one inpatient bed for patients assigned PCA. Should a patient with an agreement wish to be admitted, they only have to contact the inpatient ward, any time of the day, any day of the week. In case the inpatient bed is already occupied, the patient is put on a waiting list. If more immediate care is required, the patient can always be admitted as usual. All admissions are managed by a nurse with delegated responsibility from the head of clinic. During admission, the patient is assessed with regard to suicidality, violence, and vital parameters, such as blood pressure and body temperature. Should there be an increased risk (eg, suicidal ideation and physical injury), regular intake is made. Once admitted, patients are offered care according to their specific needs and individual care plan. Consultation with a medical doctor is possible, but not part of usual practice. The patient is also free to discharge at will, which is also handled by a nurse; however, should the patient warrant further stay at the inpatient ward, a medical doctor can decide if regular admittance is necessary.

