Since PCA is part of regular healthcare, patients can always agree to its use but refuse to participate in the present research study. The offer to take part in a study on the effects of PCA is always made after the use of PCA first has been agreed on, whereupon the objectives of this study is discussed verbally and information is provided in writing. Informed consent is required and documented in the medical records. For adolescents, informed consent needs to be signed by both the adolescent and all caregivers (eg, legal parents, custodians or other entities responsible for the patient’s care). Following this, the patient completes the self-reported outcome questionnaires that are included in the study, as reviewed below. For adolescents, this also involves the caregivers’ perception of the patient’s well-being. All of the self-reported outcome questionnaires are then completed at the mandatory yearly assessments, except for the Visual Analogue Scales (VAS) that are administered each month via SMS (more information provided under self-reported outcomes). This is in line with the procedures surrounding the use of PCA in Region Stockholm, where mandatory yearly assessments are made to check-up on patients’ health status and whether or not PCA should be continued. This is also believed to improve data collection as it does not require paper-and-pencil administration or letters.

The implementation of PCA throughout Region Stockholm is coordinated and supported by the Centre for Psychiatry Research, which is a R&D centre run jointly by Karolinska Institutet and the hospital sector. The Centre for Psychiatry Research performs an assessment of the risks and needs of each outpatient unit and inpatient ward, and provides training and supervision regarding all of the PCA routines. This consists of an online course and a half-day on-site workshop, and the latter of regular meetings with all of the healthcare providers. The Centre for Psychiatry Research is also responsible for evaluating the effects of PCA and has a research steering group consisting of the authors of the current study protocol. These range from doctoral candidates to senior-level researchers with comprehensive experience of conducting both quantitative and qualitative studies in a psychiatric setting.

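### The cost definitions count care delivered and name neither PCA training and supervision nor unused designated bed capacity, although the conclusion is about implementing PCA

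*Protocol article*

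**What the plan says.** In the protocol article, the health-economic paragraph under Statistical analysis defines two categories. The first reads "Direct costs are the expenditures associated with each visit to a psychiatric emergency department, inpatient care and involuntary care". The second reads "Total healthcare costs are the expenditures of other types of healthcare, for example, visits to primary care". On prices it says "Such expenditures are calculated from standardised price estimates provided by Region Stockholm", "resulting in an approximation of how expenditures change following the implementation of PCA". QALYs are to be derived from the EQ5D-5L, and on the comparator the text says "This will be compared to matched patients using registries". Sensitivity analyses with 50%, 75% and 95% confidence ellipses are planned around the cost-utility estimates.

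The programme's own resources are described elsewhere. Procedure states "Each inpatient ward has allocated at least one inpatient bed for patients assigned PCA", and Setting puts the number of wards at about 45. Procedure also says that a research and development centre assesses the risks and needs of each unit and trains and supervises it. Of the training it says "This consists of an online course and a half-day on-site workshop"; supervision takes the form of regular meetings. The secondary research questions ask how healthcare expenditures are affected for patients assigned PCA.

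**The concern.** The conclusion concerns what happens to expenditure once PCA is implemented, but the inputs are defined by care that takes place. Staff training is not a type of patient healthcare. A designated bed that stands unused generates no stay to price. Both resources exist because of PCA, and a comparator patient outside the programme does not draw on them.

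For cost-utility there is a further asymmetry. The Introduction suggests that patients may benefit from having access to PCA even when they seldom use it. Such a benefit would enter the QALYs through the EQ5D-5L, while the standby capacity behind it could go uncosted. The planned ellipses would not reveal this, since they describe uncertainty in the costs that were entered.

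At stake is whether a saving from fewer inpatient days, which the study hypothesises, can be read as a saving from the programme.

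**Working it through.** **Figure to reproduce.** The article gives no cost figure. Its one power figure, d = 0.12 for 564 patients, does not bear on this point.

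**Step 1: programme resources against the cost categories.**

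| Resource | Where described | Named in direct costs? | Named in total costs? |
|---|---|---|---|
| Emergency visits, inpatient and involuntary care | Statistical analysis | Yes | – |
| Other care, such as primary care | Statistical analysis | – | Yes |
| PCA training and supervision | Procedure | No | No |
| Unused time of designated PCA beds | Beds: Setting, Procedure | No | No |

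**Step 2: designated capacity.** Inputs are about 45 wards (Setting) and at least one bed per ward (Setting, Procedure).

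45 × 1 × 365 = 16,425 bed-days a year.

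This is the minimum designated capacity, occupied or not. With about 12 consenting patients per ward (Sample size calculation), it is 365 / 12 = 30.4 bed-days per participant-year.

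**Step 3: what unused time could amount to.** The article does not give occupancy, so the range below is assumed. So is 24 PCA patients per bed, which allows for patients who use PCA but are not in the analysis.

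Unused days per patient-year = 365 × (1 − occupancy) / patients per bed

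| Assumed occupancy | 12 per bed | 24 per bed |
|---|---|---|
| 30% | 21.3 | 10.6 |
| 50% | 15.2 | 7.6 |
| 70% | 9.1 | 4.6 |
| 85% | 4.6 | 2.3 |
| 100% | 0 | 0 |

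**Step 4: when this would matter.** Suppose PCA saves x inpatient days per patient-year (assumed), with 12 patients per bed and an unused day valued like an occupied one. Unused days then offset the saving if occupancy is below 1 − 12x/365:

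- x = 5: 1 − 60/365 = 0.836, about 84%.
- x = 10: 1 − 120/365 = 0.671, about 67%.

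Subtracting the variable cost avoided on an unused day, or spreading the cost over more patients, lowers both thresholds.

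**Step 5: could the beds be full?** Procedure gives a typical ceiling of 4 days, three times a month, so 4 × 3 × 12 = 144 days per patient-year. Then 365 / 144 = 2.5 patients at the ceiling would fill a bed, and 12 patients would fill it at 30.4 / 12 = 2.5 days each per month. High occupancy is therefore possible, and the bed component could be near zero. Training and supervision would remain.

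**The case against.** The strongest reply is that the article condenses a fuller plan and calls its result an approximation. The words about each visit may attach only to emergency visits, with inpatient care named as a broad category. The research question is about expenditures for patients assigned PCA, which patient-level costing can answer. This narrows the point but does not remove it: the article itself fixes both categories, and its stated conclusion is about implementation.

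Other parts of the reply stand and limit what can be claimed:

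- **Idle beds.** A reader might infer that 16,425 bed-days go unpriced. No text says that beds are added or held empty; they are designated. Procedure provides a waiting list for when the bed is taken. The remark that "few patients will use the possibility to admit themselves to inpatient care" explains skewness and gives no occupancy. Patients who decline the research, and earlier PCA users who are not analysed, may share the bed.
- **Prices.** What the regional price contains is not shown. It may include average vacancy, although a uniform price would not capture extra idle time specific to designated beds.
- **A fully costed comparator.** A reader might infer that usual care is costed in full and only PCA is not. One price source is described for all care, so nothing supports that. PCA has also run in the region since 2014 for some diagnoses, so some standing PCA cost may fall in the earlier period.
- **Overall bias towards PCA.** A reader might infer that the whole comparison favours PCA. Procedure says nurses manage PCA admissions and discharges and that consulting a doctor is not usual practice. A standard price could overstate such stays, which works against PCA.
- **Start-up costs.** Leaving out the training cost of a policy already decided is an arguable choice of perspective, but the perspective is not stated.

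**Conclusion.** The point holds in a limited form. As written, the cost definitions leave PCA training and supervision, and any unused designated bed capacity, outside the cost and cost-per-QALY results, while those results are to describe the effect of implementing PCA. Taken alone, the omission makes PCA look cheaper. That direction assumes that the matched patients are outside the programme and that the regional price does not already cover these items.

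The size cannot be computed. Over the assumed range, unused bed time runs from 0 to 21.3 days per participant-year at 12 patients per bed, which is enough to rival a saving of 5 or 10 days but equally consistent with no effect. The documents do not settle the net direction of all pricing errors. The point affects a secondary question and leaves the primary hospitalisation outcomes untouched. It merits a change because the remedy is cheap and the result would inform a region-wide policy.

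**What to change.** Add to the health-economic paragraph under Statistical analysis:

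> Cost and cost-utility results will be reported with and without PCA programme costs. These comprise PCA training and supervision, and designated PCA bed-days that were unoccupied and not otherwise used, net of avoidable variable cost and of any vacancy already included in the regional price. They will be allocated over all patients with a PCA agreement, whether or not they consented to the research, and varied over observed occupancy in the sensitivity analysis.

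This needs ward-level occupancy of the PCA beds, the coordinating centre's training and supervision costs, and a statement from the region of what its standard price contains. The extra analysis is small. The drawback for the sponsor is that the stated saving may become less favourable.
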